### *Adoption*

Both qualitative and quantitative analyses will be used to assess adoption. *Qualitative methodology* will be used to explore themes and attitudes associated with *actual* PSM implementation experiences. A sample of participants who implemented PSM will be invited to participate in individual interviews using a semi-structured interview template. Qualitative

analysis of patient interview transcripts will be performed to identify emerging “adoption” outcome themes using an inductive approach. Two investigators will independently review anonymized transcripts line-by-line, annotating passages of text with code to help catalog key concepts. Disagreements between reviewers will be resolved through discussion or by a third reviewer when necessary. Additional participants will be interviewed until it is evident that new themes are unlikely to emerge from further interviews (i.e., saturation). Participant demographic data will be summarized using descriptive statistics. ATLAS.ti, a qualitative data management program (ATLAS.ti Scientific Software Development GmbH, Berlin, Germany), will be used to facilitate the organization, management, coding, and thematic analysis of qualitative data.

*Quantitative methodology* will be used to identify characteristics associated with willingness to participate in the PSM implementation study. Participant characteristics will be entered into multivariable logistic regression models to identify variables that are independently associated with willingness to participate in the PSM phase of the study. The comparator group for this outcome will be patients who declined study participation. Variables collected for each patient will include age at time of the study participation invitation, gender, race, ethnicity, indication(s) for warfarin therapy, duration of warfarin therapy at time of study participation invitation, and warfarin tablet strength being used at time of study participation invitation.

#### *Implementation (Fidelity)*

Self-reported INR values measured during the 6-month follow up period will be individually assessed for fidelity to key PSM elements as described below. For enrolled participants actively engaged in PSM, the percentage of INRs independently and appropriately managed by the participant (i.e., participant used INR to determine warfarin dosing plan while neither contacting a clinician nor taking actions deemed inappropriate by clinicians) will be calculated. Adherence to key PSM elements will be categorized as adherent or nonadherent for each INR. Data for this outcome will be censored on the date of PSM failure or the study end-date, whichever comes first. INRs tested within  $\pm 3$  days of the date specified by PSM

participants will be categorized as fully adherent and INRs measured >3 days before or after as nonadherent. Adherence to warfarin dose selection recommendations as specified by the My Warfarin online decision support tool will be evaluated for each INR. Warfarin doses within  $\pm 5\%$  of the specified dose recommendation based on the INR result will be considered adherent.

For “implementation” outcomes, the percentage of INRs falling into adherent and nonadherent categories will be calculated for each patient using the total number of INRs performed during the PSM phase as the denominator. The mean (standard deviation) percentages for each adherence category will be summarized, stratified by implementation site, and compared using ANOVA. An omnibus P-value  $< 0.05$  will be considered statistically significant and multiple comparison tests used to determine if significant differences exist between specific sites if needed.

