## Participant clinical decision support tools

Participant clinical decision tools for the PSM implementation toolkit will consist of an online dosing tool ("My Warfarin") and a manual dosing method ("DIY dosing"). Participants or their caregivers will also be allowed to make warfarin dosing decisions based on their own

experience without using formal clinical decision support tools if desired. Participants will be instructed to contact their anticoagulation clinician in high-risk situations (e.g., INR <1.5 or >5.0, any bleeding or thromboembolic symptoms, prior to scheduled invasive procedures) or if they want to consult with a clinician for any reason.

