#### PSM implementation phase

Prior to initiating PSM, consenting participants will complete an online survey hosted in REDCap containing the following: 1) the anticoagulation knowledge tool (AKT), a validated 28-item instrument that assesses participants' anticoagulation knowledge; 2) the anti-clot treatment scale (ACTS), a 15-item participant-reported instrument assessing satisfaction with anticoagulant treatment that includes a 12-item Burdens scale and a 3-item Benefits scale; and 3) the Short Form 36 questionnaire (SF-36), a validated instrument used to estimate health-related quality of life.

Participants will complete the previously described interactive online educational module in preparation for initiating PSM. Clinician study team members at each site will use the combination of each participant's PSM knowledge assessment score, comfort level with PSM, and their subjective assessment of the participant's likelihood of success with PSM to determine if they should progress to the "spotters ready" phase where clinicians will provide feedback on the participant's warfarin dosing plans as needed. The "spotters ready" phase will end and the formal PSM phase begin once participants express feeling comfortable starting PSM on their own.

During the 6-month PSM phase, participants will be asked to check INRs every 1 to 2 weeks when INRs are in range and weekly when INR are out of range. Participants will be asked to use clinical decision support tools from the implementation toolkit (My Warfarin, DIY) or use their own experience to make independent warfarin dosing decisions. Participants will be asked to contact clinicians in high-risk situations as previously described or when additional advice is desired.

During the PSM phase, participants will self-report INR results, warfarin dosing decisions, the method used to arrive at dosing decision (i.e., My Warfarin, DIY, or using their own judgement), factors potentially impacting INR response (i.e., changes in other medications, diet, and/or health status), and bleeding/ thromboembolic complications using the previously described online data collection form hosted in REDCap.

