| 5. Value of INR being reported?                                                                     | -Patient enters INR value                                                                                                                                                                                             | If INR is 5.0 or higher, patient instructed to contact their anticoagulation provider                                                                                                       |
| 6. Based on your INR value, do you plan on adjusting your weekly warfarin dose?                     | -Yes
-No                                                                                                                                                                                                           | If "No" survey skips to question 20                                                                                                                                                         |
| 7. In response to this INR, who ultimately decided the new warfarin dose you will take?             | -I did
-Someone else/healthcare provider
-Other                                                                                                                                                                 | If "I did", question 8 is asked; otherwise, survey skips to question 9                                                                                                                      |
| 8. How did you decide which warfarin dose to take?                                                  | -My warfarin website tool
-My own decision
-Other                                                                                                                                                               |                                                                                                                                                                                             |

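### Two fidelity components score some protocol-compliant INRs as failures: dose adherence is judged against My Warfarin alone, and instructed clinician contact forfeits credit

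*Protocol*

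**What the plan says.** **Conduct rules.** The section Participant clinical decision support tools supplies two tools, My Warfarin (online) and DIY dosing (manual). It also lets participants or caregivers decide from their own "experience without using formal clinical decision support tools if desired". The PSM implementation phase section repeats the three options: participants are asked to "use clinical decision support tools from the implementation toolkit (My Warfarin, DIY) or use their own experience to make independent warfarin dosing decisions". It adds that the method behind each dosing decision will be self-reported, and it names DIY as one of the methods. On contact, the tools section states: "Participants will be instructed to contact their anticoagulation clinician in high-risk situations". The PSM implementation phase section repeats this and also allows contact whenever advice is wanted.

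**Scoring rules.** The Implementation (Fidelity) section has three parts:

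- The percentage of INRs managed independently and appropriately. An INR qualifies only if the participant set the dosing plan while "neither contacting a clinician nor taking actions deemed inappropriate by clinicians".
- Recheck timing, within 3 days of the date the participant specified.
- Dose adherence: "Adherence to warfarin dose selection recommendations as specified by the My Warfarin online decision support tool will be evaluated for each INR". A dose within 5% of that recommendation is adherent.

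Adherent and nonadherent percentages are calculated per patient over all INRs in the PSM phase, then compared across sites by ANOVA.

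**Data capture.** In the supplementary REDCap survey, the method item is "8. How did you decide which warfarin dose to take". Its options are the My Warfarin website, the participant's own decision, or other.

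**The concern.** Fidelity should tell the reader how far participants did what the programme asked of them. Here the scoring standard is narrower than the conduct standard in two places. A participant who applies the study's own DIY tool correctly, or doses from experience as allowed, is measured against a tool that they were free not to use. A participant who calls the clinic because the protocol says to do so loses credit for that INR.

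At stake is how the Implementation results are read. Percentages below 100 would mix real departures with permitted or instructed behaviour, and the protocol gives no way to separate the two. The between-site comparison of dose adherence would carry the same mixture. In a study meant to inform others about the usability of the tools and about safe self-management, that could understate how well participants followed the programme. The scoring is fixed in the protocol text, so this is not a detail left open for an analysis plan.

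**Working it through.** The protocol states no figure for this point, so there is nothing to reproduce. The check compares the rules and then applies simple arithmetic.

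**1. Dose rule against conduct rule.** Three methods are permitted, one serves as the benchmark, and the denominator is every PSM-phase INR. DIY has no adherence standard of its own. A DIY or own-judgement dose is therefore adherent if it falls within 5% of My Warfarin and nonadherent otherwise, however correctly the permitted method was applied.

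**2. Can the method be recovered from the survey?** Only in part.

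- Question 8 does not list DIY, although the PSM implementation phase section says that DIY is recorded.
- Question 6 (is a dose change planned?) sends a No to question 20, so no method is recorded at an INR where the dose is kept.
- Question 7 (who decided?) goes to question 8 only if the participant decided; otherwise it goes to question 9.

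My Warfarin use is thus identifiable only for self-decided dose changes.

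**3. Size of the dose effect (assumptions, not protocol figures).** Let s be the share of INRs dosed by DIY or own judgement, and d the share of those more than 5% from My Warfarin. If every My Warfarin user complies fully, the score under full protocol compliance is 100 × (1 − s × d):

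| s | d = 10% | d = 30% | d = 50% |
|---|---|---|---|
| 25% | 97.5 | 92.5 | 87.5 |
| 50% | 95.0 | 85.0 | 75.0 |
| 75% | 92.5 | 77.5 | 62.5 |

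Two fully compliant sites with s = 25% and s = 75%, both at d = 30%, would differ by 92.5 − 77.5 = 15.0 points through method choice alone. The protocol does not say that sites will differ in this way.

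A difference above 5% need not be a large one. Participants use a single tablet strength. If half a tablet is the smallest step (an assumption), one half-tablet per week is 0.5/7 = 7.1% at 7 tablets per week, 0.5/9 = 5.6% at 9, and 0.5/10 = 5.0% at 10.

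**4. Size of the contact effect.** Testing every 7 to 14 days over six months (taken as 182 days) gives 182/7 = 26 to 182/14 = 13 INRs per participant. One instructed contact lowers that participant's independent-and-appropriate percentage by 1/26 = 3.8 to 1/13 = 7.7 points. Three contacts lower it by 3/26 = 11.5 to 3/13 = 23.1 points. How often instructed contact will occur is not stated.

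**The case against.** The best defence is that each measure does what its literal description says. Agreement with one common benchmark over all INRs is a reasonable way to describe concordance with My Warfarin, and an INR handled with a clinician's help was not handled independently. Both points stand. They do not justify calling the first measure adherence when other methods are permitted, or leaving instructed contact indistinguishable from elective contact and inappropriate action.

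Several stronger readings are tempting, and the protocol does not support them:

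- A reader might infer that any DIY or own-judgement dosing is nonadherent. It is so only when the dose is more than 5% from My Warfarin.
- A reader might infer that clinician contact is scored nonadherent and enters the ANOVA. The text never labels it so, and it is unclear whether the independent-and-appropriate percentage feeds the adherence categories.
- A reader might infer that a high-risk INR fails whatever the participant does, or that the measure rewards ignoring the instruction. These two cannot both hold. Whether non-contact is inappropriate is left to clinicians' judgement, so neither outcome is fixed by the text.
- A reader might conclude that the whole fidelity outcome is invalid, or that the ANOVA detects tool preference instead of fidelity. Recheck timing is untouched, and a shift common to all sites cancels between sites. A partial reflection of method choice is the most that can be claimed.
- A reader might say that the methods can never be separated. My Warfarin is its own option wherever question 8 is asked, the final survey asks which tools were used, and question 21 takes free text. The gap is real but partial.

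**Conclusion.** The concern holds for two of the three fidelity components. Following the protocol exactly would score some fully compliant INRs as nonadherent on dose, and would deny credit to INRs where the participant made the contact that the protocol instructs.

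The contact effect is 3.8 to 7.7 points per contact, given 26 to 13 INRs over 182 days. It is larger for anyone censored early for PSM failure, who has fewer INRs. The dose effect cannot be sized from the protocol. The span of 97.5% to 62.5% rests wholly on the assumed ranges for method use and disagreement, and on full compliance among My Warfarin users. Site differences in dose adherence may partly reflect method choice. The primary implementation outcome, successful transition to PSM, does not depend on these scores. The problem is therefore one of interpreting a secondary result, and it is worth correcting because the correction is cheap.

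**What to change.** Reconcile the Implementation (Fidelity) section with the two conduct sections by changing scoring and data capture only. No change to any clinical rule is proposed.

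- **Dose.** Report agreement with My Warfarin over all INRs under the name concordance. Report adherence to My Warfarin only for INRs dosed with it, score DIY INRs against the DIY method, and show own-judgement INRs separately.
- **Method.** Add DIY to the method question and ask that question at every INR, including when no dose change is planned. Adding the option alone is not enough, because the skips in questions 6 and 7 would still leave the method unrecorded at many INRs. Enrollment began in March 2023, so this helps only prospectively. Earlier INRs with no recorded method form an unknown class.
- **Contact.** Report INR management in three classes: independent and appropriate; escalated as the protocol instructs; and other (elective contact or inappropriate action). Count the first two as faithful and still show the independent share. Elective contact is permitted, so keep the two parts of the last class visible.
- **Trigger.** The tools section gives an INR above 5.0 as an example of when to contact, while the survey gives the instruction at 5.0 or higher. The two must be reconciled before the escalated class can be defined.

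The cost is protocol wording, slightly more tabulation, and the method question asked at every INR. My Warfarin adherence will also rest on fewer INRs.

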## Patient selection criteria

General PSM patient selection criteria will include 1) medical stability at the time of PSM initiation; 2) cognitive stability and capable of following instructions and/or has a willing and capable caregiver; and 3) currently self-testing with a home INR device. Specific PSM patient selection criteria related to participation in the PSM implementation study will include 1) goal INR range of 2.0 to 3.0 or 2.5 to 3.5; 2) completed more than 9 months of warfarin therapy at time of enrollment; 3) willing to use single warfarin tablet strength; 4) planned duration of warfarin therapy of at least 6 months; 5) willing to test INR every 7-14 days; 6) receiving majority of care within the enrolling site's healthcare system; and 7) able to maintain internet access throughout study participation.

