| 20. When do you plan on rechecking your next INR?                                                                                               | -Patient enters date of next INR                                         |                                                                                                          |
| 21. Is there anything else you wanted to tell us about today's INR?                                                                             | -Text box for patient comments                                           |                                                                                                          |

INR-international normalized ratio; PSM-patient self-management; VAMC-Veterans Administration Medical Center; ID-identification

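### Test-timing adherence is scored against the participant's own recheck date and only over INRs performed, so it does not measure adherence to the protocol's testing interval

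*Protocol*

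**What the plan says.** Implementation (Fidelity) fixes three things about test timing.

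- **Unit.** "Self-reported INR values measured during the 6-month follow up period will be individually assessed for fidelity to key PSM elements". A test that was never done is not a unit.
- **Reference date.** The window is 3 days either side, counted in "days of the date specified by PSM" participants. INRs in the window reported by these "participants will be categorized as fully adherent and INRs measured >3 days before or after as nonadherent".
- **Denominator.** Each patient's percentage is computed "using the total number of INRs performed during the PSM phase as the denominator". The data are censored at PSM failure or study end, whichever is earlier. The percentages are then summarised by site and compared by ANOVA.

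The participant's date comes from item 20 of the REDCap survey in the Supplementary material: "When do you plan on rechecking your next INR". It is a date entry with no stated limit on how far ahead it may lie.

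The testing interval is set elsewhere. Under PSM implementation phase, participants are asked to "check INRs every 1 to 2 weeks when INRs are in range and weekly when INR are out of range". Under Patient selection criteria, they must be "willing to test INR every 7-14 days". Nothing in the fidelity section refers to either statement, and no count of expected or missed tests is defined.

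**The concern.** The protocol asks for a testing interval and then scores timing in a way that cannot show whether it was followed. Two features combine.

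- **Reference date.** A participant who books the next INR well beyond 14 days and keeps the date is fully adherent.
- **Denominator.** A test not done never enters the denominator. If the participant later resumes, the whole lapse shows up as one late INR. If no further INR comes before censoring, it does not show at all.

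The Discussion says the study will inform on whether US patients can engage in PSM safely. A timing figure that can read 100% under sparse testing would be easy to misread as evidence that the requested interval was kept.

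**Working it through.** The protocol gives no figure for this outcome, so there is none to reproduce. The check applies its rule to simple test histories and rescores them against the protocol's own interval.

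**Inputs from the protocol**
- Window: 3 days either side of the participant's date (Implementation (Fidelity)).
- Maximum interval: 14 days in range, 7 days out of range (PSM implementation phase).
- Follow-up: 6 months of PSM (Reach).

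**Assumptions**
- 6 months = 26 weeks = 182 days, with the clock starting at an in-range INR on day 0.
- INRs always in range and no PSM failure declared.
- The histories themselves; the protocol gives no rate of missed tests.

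**Formulas**
- As written: INRs within 3 days of the self-set date ÷ INRs performed.
- Against the interval: due INRs done ÷ INRs due. At the 14-day maximum, 182/14 = 13 are due (weeks 2, 4, …, 26).

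**Histories**
1. *Every recheck set at 28 days and kept.* 182/28 = 6.5, so 6 INRs are done, all on the self-set date.
2. *Two-weekly plan: six on time, a 10-week gap, then three more.* Tests are done at weeks 2 to 12, then at 22, 24 and 26. As written, the week-22 INR is 8 weeks late against its week-14 date and is the only nonadherent one: 6 + 2 = 8 of 9. Against the interval, weeks 14, 16, 18 and 20 are missed: 13 − 4 = 9 done. The week-22 INR falls on a due date and counts as done.
3. *Two-weekly plan: four on time, then none.* Four INRs performed, all adherent.

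| History | As written | Against tests due |
|---|---|---|
| Kept 28-day rechecks | 6/6 = 100% | 6/13 = 46% |
| Six on time, 10-week gap, three more | 8/9 = 89% | 9/13 = 69% |
| Four on time, then none | 4/4 = 100% | 4/13 = 31% |

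**Sensitivity**
- If weekly testing were due throughout, 182/7 = 26 tests are due and the first history gives 6/26 = 23%.
- The 13th due date falls on the last day. Leaving it out gives 6/12 = 50% for the first history and 4/12 = 33% for the third.
- The third history depends on failure not being declared. If failure were declared at week 8, only 4 tests would have fallen due and both scores would be 100%.

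**The case against.** Several points on the other side have force.

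- **Keeping one's own recheck date is a reasonable thing to measure in self-management.** This stands. The present measure should stay, under a label that says what it is.
- **INRs performed is the natural denominator for other fidelity outcomes.** This stands. Dose adherence and independent management are judged INR by INR. A reader might infer that the denominator is wrong throughout the section; the point is confined to test timing.
- **Stopping testing has consequences elsewhere.** This stands in part. A reader might infer that someone who stops loses nothing. Reach counts a declared PSM failure and records its timing and reasons, and censoring would end the due count too. However, the protocol does not say that a lapse in testing is itself a failure.
- **Clinicians see the survey summaries and can judge actions inappropriate.** This stands in part. An overlong recheck date could be caught under independent and appropriate management, though the text does not say so. A test not done generates no survey and no summary.
- **Participants already self-test and accept 7 to 14 days.** That makes long lapses less likely. Their frequency is unknown.
- **The interval is a range that depends on the last INR, so due tests are not defined by it alone.** This stands. A counting rule is needed and is given under the fix.

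Two stronger readings lack support. One is that under-testing is the main fidelity failure; the protocol lists several elements and ranks none. The other is that the site ANOVA is biased; it is distorted only if under-testing differs by site, and nothing shows that it does.

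**Conclusion.** The point holds for test timing. The protocol itself fixes the reference date and the denominator, so this is a stated rule with a misleading result and not a detail left to a later plan. The measure captures adherence to self-set dates, and it cannot show adherence to the interval in Patient selection criteria and PSM implementation phase.

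In the illustrations the gap between the two scores is 20 to 69 percentage points (89% against 69%; 100% against 31%). These figures assume 26 weeks, always in range, a 14-day maximum and no declared failure. They show what the rule allows; a reader might take them as the expected overstatement in this study, but the protocol gives nothing from which to estimate that. A missed test is also not always invisible: if an INR follows more than 3 days after the planned date, it counts once as nonadherent.

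The primary Reach outcome does not use this percentage. The change is worth making, but the study does not depend on it.

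**What to change.** For test timing only, add a per-participant measure: due INRs done within the 3-day tolerance, divided by INRs due from PSM start to censoring. State the counting rule:

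- Count each due INR from the last INR, using the maximum interval the protocol already states: 14 days after an in-range INR, 7 days after an out-of-range one.
- Each further interval of that length without an INR counts as one missed test.
- An INR earlier than the maximum meets the due test, because the protocol allows weekly testing in range. The tolerance therefore matters on the late side. An INR between two due dates meets the next one and restarts the count.
- Say whether a due date whose tolerance is still open at censoring is counted.

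Use this measure in the site summary and ANOVA for testing adherence. Keep the present measure, labelled as adherence to the self-set recheck date. Keep INRs performed as the denominator for dose adherence and independent management.

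The testing schedule does not change. Goal range, INR date, INR value and planned recheck date are already collected (survey items 3, 4, 5 and 20). The cost is wording, some programming and a lower reported percentage.
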